### Randomization

During the 2-week lead-in period, participants will be randomized to either the pulse based diet or control TLC diet. Participants will be notified of diet allocation via email (and are not blinded). Randomization will be performed by an investigator who is not involved in obtaining or entering participant data. Randomization will be stratified based on the current use of the insulin sensitizing drug Metformin, using a computer-generated allocation schedule with a block size of 4.

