## Methods

### Design overview

The present study is a single-blind, parallel, stratified-randomized clinical trial. The work is funded by Saskatchewan Pulse Growers and Agriculture Agri-Food Canada. The study design is detailed in Fig. 1. The aim of the study is to determine the effect of a pulse-based diet compared to a healthy control diet on disease measures related to PCOS as well as metabolic syndrome risk factors in women with PCOS while they are enrolled in an exercise program. After the study coordinator obtains informed signed consent, study participants will be assessed to determine whether they have PCOS. Women diagnosed with PCOS will undergo baseline testing followed by a 2-week lead-in period on the healthy control diet (therapeutic lifestyle changes (TLC) recommended by the National Cholesterol Education Program). Following the lead-in, participants will repeat baseline blood measures followed by randomization to either the pulse-based diet or the TLC diet for 16-weeks while participating in an aerobic exercise program. Blood measures will be assessed after 9-weeks and at the end of the 16-week intervention, participants will undergo end of intervention testing; follow-up measures will also be assessed at 6-months and 12-months.

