### Sample size

A pilot study (unpublished) was carried out on preliminary data from 41 women with PCOS randomized to the pulse-based or TLC diet. Thirteen of the 41 women dropped out of the study giving a dropout rate of 32%. Changes in fasting glucose following the intervention (*n* = 28) was used to determine the required sample size for recruitment into the study. Changes in the mean fasting glucose were -0.18 and 0.14 mmol/L for the pulse-diet group and TLC group, respectively, with a population standard deviation of 0.46 and an effect size of -0.70. The pilot data provided 80% power for detecting a significant difference in fasting glucose concentration between groups (*p* < 0.05) following the intervention. It was determined 34 participants per group would be required for the study. Due to the dropout rate of 32%, the recruitment of 100 participants (i.e. 50 per group) was determined necessary.

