### Intervention

Following the 2-week lead-in phase, participants will be randomized to either the pulse-based diet or TLC diet and commence the 16-week diet and exercise intervention. The 16-week time period is based on a review of pulse-based diets for improving insulin and glucose levels [11]. In addition, the length of intervention is required to observe changes in outcome measures related to fertility. After 4-weeks of intervention, participants will meet with the study coordinator to discuss any difficulties with participating in the study and hand in the first 4-weeks of study documents which include the daily food and exercise log as well as a 1-day food record and leisure-time exercise questionnaire. After 9 weeks of the intervention, blood will be collected for clinical measures of reproductive hormones and metabolic syndrome risk factors. At the end of the 16-week intervention, baseline measures will be repeated.

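### A single fixed block size of 4 could make up to one third of allocations certain to staff who know it and all earlier allocations in the stratum

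*Protocol article*

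**What the plan says.** The Randomization section gives one constant block length: "using a computer-generated allocation schedule with a block size of 4". There is one stratification factor with two levels: "Randomization will be stratified based on the current use of the insulin sensitizing drug Metformin". Allocation is 1:1, since under Sample size "the recruitment of 100 participants (i.e. 50 per group) was determined necessary". The Setting section names one city.

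The person who assigns is kept apart from the data: "Randomization will be performed by an investigator who is not involved in obtaining or entering participant data". Participants are told their diet: "Participants will be notified of diet allocation via email (and are not blinded". Design overview labels the trial single-blind, and Data management and analysis plans coding to blind those who collect and analyse data.

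The coordinator appears at both ends of the process. Design overview has this role take consent: "After the study coordinator obtains informed signed consent". Recruitment has the same role promote the study to primary care physicians. Under Intervention, after 4 weeks, "participants will meet with the study coordinator to discuss any difficulties with participating in the study", and hand over their daily logs. Compliance requires the pulse group to log the pulse meals eaten, so those logs show the arm. Supplied meals are collected weekly at the exercise facility (Diet).

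**The concern.** Concealment needs more than a list held by someone independent. The next assignment must also not be deducible from those already made. A short constant block in few strata at one place is the arrangement in which deduction is easiest, and here a role that brings women into the study also comes to learn past assignments.

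If staff could tell what the next entry would be, the timing or order of entry could be influenced by it. The groups could then differ at baseline in ways that covariate adjustment cannot be relied on to remove. Scope for judgement remains after consent: diagnosis, baseline testing and the lead-in follow it, and one exclusion in the Population section concerns conditions that limit eating a pulse diet, which bears on one arm only.

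**Working it through.** **Inputs from the protocol article.** Block size 4; two Metformin strata; 1:1 allocation; 100 participants, which the plan's own figures reproduce as 34/(1 − 0.32) = 50 per group. The article states no predictability figure, so there is none to reproduce.

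**Ceiling: every earlier allocation in the stratum known at once, with block size and block starts known.** A position is certain when one arm is already used up in the block. There are six equally likely blocks.

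- AABB and BBAA: positions 3 and 4 are certain, 2 each.
- ABAB, ABBA, BAAB and BABA: only position 4 is certain, 1 each.
- Certain share = (2 × 2 + 4 × 1)/(6 × 4) = 8/24 = 33.3%. By position: 0, 0, 1/3, 1.

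With two strata, 100 women and incomplete last blocks, simulation gives about 32.5% for Metformin shares from 10% to 50%.

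**Best guess (name the arm with fewer entries so far, toss a coin on ties).** The chance of being right by position is 1/2, 2/3, (1/3 × 1 + 2/3 × 1/2) = 2/3, and 1. The mean is (1/2 + 2/3 + 2/3 + 1)/4 = 17/24 = 70.8%, against 50% under simple randomisation.

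**Delayed knowledge.** The article gives neither the recruitment period nor the Metformin share. Assumptions: 100 women arriving at random over 1 to 5 years, 20% on Metformin, block size and block starts known, and each earlier allocation learned a fixed number of weeks after that woman's entry. Simulated share of certain allocations:

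| Delay | 1 year | 2 years | 3 years | 5 years |
|---|---|---|---|---|
| 0 weeks | 32.5% | 32.5% | 32.5% | 32.5% |
| 1 week | 12% | 20% | 23% | 27% |
| 2 weeks | 5.5% | 12% | 17% | 22% |
| 3 weeks | 3% | 8% | 12% | 18% |
| 6 weeks | 1% | 3% | 5% | 10% |

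One week corresponds to a first weekly meal pick-up, counting from randomisation. Six weeks is the 2-week lead-in plus the meeting after 4 weeks of intervention, counting from consent at the start of the lead-in. The relevant starting point is itself unsettled: Randomization places assignment during the lead-in, while Design overview and Intervention place it afterwards.

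**With randomly varying sizes, staff knowing the set of sizes and every earlier allocation at once.**

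| Scheme | Certain | Best guess right |
|---|---|---|
| Fixed 4 | 33.3% | 70.8% |
| Random 4/6 | about 5.6% | about 69% |
| Random 4/6/8 | about 2.1% | about 68% |

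**The case against.** A reader might infer that recruiters in this trial can foresee one third of assignments. The article does not support that. Nowhere does it say that the coordinator knows the block size, where blocks begin, or allocations as they are made. Assignment is by a separate investigator, with notice by email to the participant. The coordinator's documented exposure is the meeting after 4 weeks of intervention, which is the slowest route in the table (about 1% to 10%). Meal pick-up is at the exercise facility, where the Exercise section places research assistants, and nothing says the coordinator is there. All of this stands, and it makes one third a ceiling.

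Steering is also harder than it sounds. Diagnosis by a specialist, baseline tests tied to cycle days for women with cyclical bleeding, and the lead-in lie between consent and assignment, so consent order need not be list order. This stands for decisions taken at consent. It has less force for decisions nearer to randomisation.

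A reader might also call the trial open. The article says otherwise: "The present study is a single-blind, parallel, stratified-randomized clinical trial". Coding is planned for data collectors and analysts, though coding does not hide the arm from someone who reads a log of pulse meals.

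Recruitment may already have been complete. Study status calls the study ongoing with follow-up still to come, and the Discussion refers to over 100 women with baseline measures against a target of 100. Publication of the block size may therefore have informed no recruiter. The article does not settle this.

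Finally, the remedy lowers best-guess success by only about 3 percentage points. That is correct: its gain is in removing certainty, not in preventing probable guesses. A condensed article may also leave access to the list to the full protocol, so silence on access is not itself a fault. The point rests on the block scheme that is stated.

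**Conclusion.** The weakness in concealment is real but modest. A constant block of 4 in two strata at one location, with unblinded participants and a recruiting coordinator who later handles arm-revealing logs, leaves some assignments open to deduction, and the independent assigner does not remove this. The size is at most one third of allocations, given full and immediate knowledge of block size, block starts and earlier allocations. It is about 1% to 27% under assumed delays of 1 to 6 weeks and recruitment over 1 to 5 years, with an assumed 20% on Metformin. Nothing in the article shows that any assignment was foreseen or that selection bias occurred.

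**What to change.** For any allocations not yet made, generate the schedule within each Metformin stratum with randomly varying block sizes, for example 4, 6 and 8. Withhold the sizes from everyone who recruits, consents or assesses until recruitment closes. Make the sections agree on whether randomisation falls during or after the lead-in. If recruitment has closed, report which roles knew the block size and which knew earlier allocations, and when.

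The cost is one new computer-generated list and slightly larger possible imbalance in an incomplete last block. Sample size and analysis do not change.

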### Baseline measures

Prior to starting the 2-week lead-in phase and intervention, all participants will undergo baseline assessments. Assessments include a transvaginal ultrasound, fasting clinical blood measures of reproductive hormones and metabolic syndrome risk factors, glucose tolerance test (GTT) including blood sample for measurement of non-clinical metabolic syndrome risk factors, anthropometric measures, dual-energy X-ray absorptiometry (DXA), physical activity assessment via accelerometer and leisure-time activity questionnaire, 4-day food record, pulse survey questionnaire, and quality of life questionnaire.

### Study phases

The study will consist of 3 phases: 1) Lead-in phase; 2) Intervention; and, 3) Maintenance.

### Lead-in phase

All participants will follow a 2-week lead-in phase with the purpose of controlling for diet variability in baseline blood measures. The lead-in phase involves an initial 1.5-h meeting with a registered dietitian who will discuss the participant’s baseline 4-day food record that will be given during assessment of other baseline measures. The dietitian will provide handouts on and explain the control TLC guidelines to each participant. The guidelines were developed by the National Cholesterol Education Program (NCEP) Expert Panel on Detection, Evaluation, and Treatment of High Blood Cholesterol in Adults [22]. Participants will also be provided with Canada’s Food Guide which gives daily recommendations of 7-8 servings of fruit and vegetables, 6-7 servings of grains, 2 servings of milk or alternatives, and 2 serving of meat or alternatives. The dietitian will explain healthy choices for each food group based on the TLC guidelines which include choosing whole grains and fiber rich foods, lower-fat milk and milk alternatives, and lean meats and meat alternatives, as well as eating less fat and choosing healthy fats more often, and limiting salt, sugar, and alcohol intake.

The lead-in approach has been used by others [23, 24] to control for differences at baseline in measures that might be influenced by previous diet (i.e., ensuring similarity in baseline measures, such as blood parameters, between the 2 groups). After completion of the 2-week lead-in period, participants will repeat the assessment of clinical blood measures of reproductive hormones and metabolic syndrome risk factors.

### Intervention

Following the 2-week lead-in phase, participants will be randomized to either the pulse-based diet or TLC diet and commence the 16-week diet and exercise intervention. The 16-week time period is based on a review of pulse-based diets for improving insulin and glucose levels [11]. In addition, the length of intervention is required to observe changes in outcome measures related to fertility. After 4-weeks of intervention, participants will meet with the study coordinator to discuss any difficulties with participating in the study and hand in the first 4-weeks of study documents which include the daily food and exercise log as well as a 1-day food record and leisure-time exercise questionnaire. After 9 weeks of the intervention, blood will be collected for clinical measures of reproductive hormones and metabolic syndrome risk factors. At the end of the 16-week intervention, baseline measures will be repeated.

### Maintenance

During the final phase of the study, participants will be followed up at 6-months and 12-months post intervention to determine if participants are continuing to follow the “standard of care” recommendations (i.e., TLC diet and exercise) and for volunteers randomized to the pulse-based diet, to determine if they continue to follow a pulse-based diet. Six-month and 12-month follow-up measures include a transvaginal ultrasound, GTT, clinical blood measures of reproductive hormones and metabolic syndrome risk factors, DXA, anthropometric measures, pulse survey questionnaire, and quality of life questionnaire. In addition, physical activity will be assessed via accelerometer at the 6-month follow up.

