**Methods:**

Women with symptoms of PCOS will be recruited for the study and a diagnosis of PCOS will be determined by an obstetrician-gynecologist. Women with PCOS will be randomly assigned to receive either a pulse-based diet or the National Cholesterol Education Program therapeutic lifestyle changes (TLC) diet for 16 weeks while participating in an aerobic exercise program. One hundred participants will be required (drop-out rate of 32%) for recruitment to provide 80% power for detecting a significant difference in fasting glucose (*p* < 0.05). Measures related to infertility, metabolic syndrome, quality of life, dietary intake and physical activity will be assessed pre- and post-intervention with follow up assessment at 6- and 12-months post-intervention.

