### Accelerometer

Physical activity and time sedentary will be objectively measured using the Actical™ (MiniMitter, Bend, Oregon) accelerometer, a uniaxial accelerometer that detects vertical acceleration. The Actical™ has been validated to measure physical activity in adults [32]. Accelerometers will be used at the beginning of the study to measure the participants’ usual activity (i.e., before exercise program). The Actical (28 x 27 x 10 mm/17 g) will be worn by the participants on a belt worn around the waist with the accelerometer situated at the hip, which will be demonstrated by a research assistant. Participants will be given the monitor on day 1 with data collection programed to record for 7 consecutive days, starting at 12:00 am on day 2 and ending at 12:00 am on day 8. Participants will be encouraged to wear the device on day 1 prior to start of data collection. The participants will be asked to wear the monitor at all times while awake, with the exception of water based activities such as bathing and swimming. The digitized values from the accelerometer are summed over a user-specified interval of 60 s, resulting in a count value per minute (cpm). Data will be downloaded and the raw accelerometer files visually screened for spurious data. Data will be processed using custom KineSoft software (KineSoft, Loughborough, UK). Wear time will be defined by subtracting non-wear time from 24 h. Non-wear time will be defined as at least 60 consecutive minutes of zero counts, with allowance for 1–2 min of counts between 0 and 100. Time spent in different intensities (i.e. sedentary, light, moderate and vigorous) will be calculated using published intensity thresholds for the Actical accelerometer [33, 34], which were used in the Canadian Health Measures Survey [35]. Total time in each intensity will be calculated as the sum of the minutes at a given intensity while the accelerometer is worn.

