### Data management and analysis

The present study will follow intent to treat analysis with measurements and analysis carried out on all participants. All identifying information will be maintained on a secure University of Saskatchewan password protected drive that is shared only with principal investigators and primary research assistants identified on our ethics submission. All hard copies of identifiable information will be securely stored in a locked filing cabinet in a locked room with restricted access. A participant coding system will be used for all data collection which will be stored separately from identifying information.

All raw data obtained will be compiled and reviewed for accuracy on an Excel Spreadsheet. Descriptive statistics will be performed for all outcome measurements for the presentation of group data as means + standard deviation as well as to identify outliers and determine normality of the data.

The treatment effect on the dependent variables will also be assessed by a group by time ANOVA (baseline, 9- and 16-weeks), with repeated measures on the time factor using Statistica (Statsoft, Chicago IL). Any missing data points at 16-weeks will be accounted for by carrying forward the 9-week value. To verify this approach, we will also run a sensitivity analysis including only participants who complete all 3 time points. Any differences determined between the groups at baseline will be used as co-variates in our analysis. Questionnaire data (Quality of Life, Pulse Consumption, Physical Activity) will be presented descriptively. The participants and group categorization will be coded such that the investigators collecting and analyzing data are blinded to which diet the participants were following.

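### The 6- and 12-month visits list no instrument for TLC diet and none for activity at 12 months, though both are to be followed up; the accelerometer dates and the quality-of-life analysis also need correcting

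*Protocol article*

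**What the plan says.** **Follow-up.** The Maintenance section gives the purpose of the 6- and 12-month visits as "to determine if participants are continuing to follow the “standard of care” recommendations (i.e., TLC diet and exercise", and, for the pulse arm, whether the pulse-based diet is kept up. It lists ultrasound, glucose tolerance test and clinical bloods, then "DXA, anthropometric measures, pulse survey questionnaire, and quality of life questionnaire". One sentence on activity follows: "In addition, physical activity will be assessed via accelerometer at the 6-month follow up". The Methods paragraph of the abstract is broader: "quality of life, dietary intake and physical activity will be assessed pre- and post-intervention with follow up assessment at 6- and 12-months post-intervention".

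**Accelerometer.** The Accelerometer section has the device "record for 7 consecutive days, starting at 12:00 am on day 2 and ending at 12:00 am on day 8".

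**Quality of life.** The Design overview names it as a secondary outcome. Data management and analysis then states: "Questionnaire data (Quality of Life, Pulse Consumption, Physical Activity) will be presented descriptively".

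**The concern.** The maintenance phase sets a question about adherence that its own measurement list cannot fully answer. For women in the control arm the TLC guidelines are the whole assigned diet, yet nothing listed at either follow-up visit measures whether they still follow them. Nothing listed at 12 months measures exercise in either arm. Ultrasound, glucose tolerance and DXA are nevertheless repeated at 12 months. If a 16-week difference has faded by then, the trial could not tell a lapse in diet or exercise from an effect that wears off despite adherence.

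The accelerometer dates contradict the stated number of days. If the dates are what is programmed, one weekday goes unrecorded for each woman, and which one depends on her start day. That matters for a weekly picture when exercise is prescribed on 5 days of the week.

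For quality of life, a named secondary outcome would be reported without an estimate of the arm difference and its uncertainty.

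**Working it through.** **1. Coverage by visit.** Inputs: Baseline measures (full baseline set), Intervention (baseline measures repeated at 16 weeks) and Maintenance (6- and 12-month list).

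| Instrument | Baseline | 16 weeks | 6 months | 12 months |
|---|---|---|---|---|
| 4-day food record | yes | yes | not listed | not listed |
| Leisure-time questionnaire | yes | yes | not listed | not listed |
| Accelerometer | yes | yes | yes | not listed |
| Pulse survey | yes | yes | yes | yes |
| Quality-of-life questionnaire | yes | yes | yes | yes |

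Counts over the two follow-up visits:
- TLC diet: 0 of 2
- activity by any instrument: 1 of 2
- pulse intake: 2 of 2
- quality of life: 2 of 2

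The pulse survey does not fill the diet gap. The Pulse consumption questionnaire section describes it as covering beliefs, barriers and current pulse intake, not adherence to TLC guidelines. The daily logs and 1-day food records in the Compliance section monitor the intervention period and are not listed for follow-up.

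Against the abstract, dietary intake at 6 and 12 months and activity at 12 months are promised but have no matching instrument, apart from pulse intake.

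**2. Accelerometer window.** Inputs: start 12:00 am on day 2, end 12:00 am on day 8, stated length 7 days.
- As written: (8 − 2) × 24 h = 144 h; 144 / 24 = 6 days.
- Stated length: 7 × 24 h = 168 h.
- Difference: 168 − 144 = 24 h; 24 / 168 = 14.3% of the stated window, if the endpoints govern.
- Other readings: with both midnights taken as the end of the named day, the window is still 6 days. Seven days results only if the two midnights are read differently (start of day 2 to end of day 8) or an endpoint is moved.
- A 7-day window from the stated start: 12:00 am on day 2 to 12:00 am on day 9 is (9 − 2) × 24 = 168 h.

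**3. Quality of life.** No arithmetic applies. The Design overview makes it a secondary outcome. The analysis section assigns the dependent variables a group-by-time ANOVA at baseline, 9 and 16 weeks, and sets questionnaire data apart for description. The Intervention section lists only blood collection at 9 weeks, so that three-time-point model would not fit this questionnaire anyway. A baseline-adjusted comparison would.

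**The case against.** The Maintenance section says its measures include the listed items, and a journal article need not be exhaustive. This carries some weight, but the list is itemised, the baseline section names the food record and leisure-time questionnaire explicitly, and the separate accelerometer sentence ties activity to one visit. At the least, the abstract and the Maintenance section disagree. It is also fair that the pulse-diet half of the maintenance question is at least partly covered.

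The window may be loose wording for the midnight that closes day 8, and the article does not show which phrase sets the device. So loss of data is not established; the contradiction is. Either reading applies to both arms, so no between-arm bias follows.

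Describing a self-reported secondary outcome without a test is defensible when participants know their diet and the sample was sized on fasting glucose. An interval estimate is still more informative than separate arm summaries, and it needs no claim of power.

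Three stronger readings are tempting and are not supported:
- *The secondary outcomes cannot be delivered.* The outcome lists tie them to no follow-up visit, and diet, activity and quality of life are all measured at baseline and 16 weeks in both arms.
- *Quality of life has no between-arm comparison.* Group means with standard deviations are planned for all outcome measurements, so the arms can be set side by side. What is missing is an estimated difference with its uncertainty.
- *Activity totals are distorted by wear time.* The article sums worn minutes ("Total time in each intensity will be calculated as the sum of the minutes at a given intensity while the accelerometer is worn"), but it also defines wear time ("Wear time will be defined by subtracting non-wear time from 24 h"). Valid-day rules and standardisation are commonly left to the full plan, and nothing in the article suggests that wear differs by arm. Any percentage would rest on invented wear patterns.

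**Conclusion.** The point holds in a limited form. Its main part is that the stated maintenance aim and the abstract go beyond the listed follow-up measures: TLC diet is uncovered at both follow-up visits and activity at 12 months. The accelerometer section contradicts itself by 24 h (6 days against 7), without implied bias between arms. Quality of life is a secondary outcome for which the plan fixes a purely descriptive analysis.

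No primary outcome, no sample-size figure and none of the 16-week diet and activity measurements is affected. The conclusion assumes that the itemised Maintenance list is complete; if the full protocol lists further follow-up instruments, the first part reduces to correcting the article. The changes should be made, but the trial's main comparison does not depend on them.

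**What to change.** 1. **Follow-up measures.** Add the existing 4-day food record and leisure-time questionnaire to the 6- and 12-month visits still to come. Giving the questionnaire at both visits keeps one activity measure common to baseline, 16 weeks, 6 and 12 months. Cost: some participant burden, mainly from the food record, and an ethics amendment. Visits already completed cannot be recovered, so report how many women have the added measures. If this is not acceptable, limit the maintenance aim and the abstract to what is measured: pulse intake at both visits and accelerometry at 6 months.
2. **Accelerometer window.** Check the device setting in use. Then either set the end to 12:00 am on day 9 or state that 6 days are recorded. If the setting changes part-way, record which window each woman had. Cost: one setting or one line of text.
3. **Quality of life.** Add a between-arm difference in questionnaire scores with 95% CI, adjusted for the baseline score, at 16 weeks and at 6 and 12 months, labelled as secondary. Cost: a few lines in the analysis plan and no new data.
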